#### Assessment of metabolic syndrome parameters and biomarkers

Blood samples will be drawn to measure the following metabolic syndrome parameters: Fasting plasma glucose (FPG), Glycated haemoglobin (HbA1c), fasting insulin. HbA1c will be measured at each visit and FPG and fasting insulin will be measured every 12 weeks, as shown in the Schedule of Study Procedures. Homeostasis Model Assessment (HOMA2) for steady state beta cell function (HOMA2-B) and for insulin resistance (HOMA2-IR) will be calculated.

Blood and urine samples will also be collected to measure pro-inflammatory/inflammatory, diabetic, obesity, and fibrotic markers. These include Interferon gamma (IFNγ), cystatin C, interleukin (IL)-6, IL-8, monocyte chemoattractant protein-1 (MCP-1), tumour necrosis factor alpha (TNFα), IL-10, vascular endothelial growth factor (VEGF), adiponectin, and glucagon in blood and Albumin/creatinine ratio (ACR) and MCP-1 in urine.

Additional pro-inflammatory/inflammatory, fibrosis, diabetic and obesity biomarkers in blood (plasma) and urine will be measured for exploratory analysis. The biomarkers to be analysed will include but are not limited to: free fatty acid (FFA), cholecystokinin (CCK), leptin, adipsin, ghrelin, resistin, visfatin, c-peptide, glucagon-like peptide 1 (GLP-1), plasminogen activator inhibitor 1 (PAI-1), gastric inhibitory peptide (GIP), alpha-1 antitrypsin (AAT), connective tissue growth factor (CTGF), intercellular adhesion molecule (ICAM-1), fibrinogen, and nitric oxide (NO) (all in plasma).

The above biomarkers will be analysed by the study site’s local research laboratory and partners as well as ProMetic BioSciences Inc.

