### Study objectives

The primary objective is to evaluate the safety and tolerability of 800 mg PBI-4050 (Investigational Medicinal Product [IMP]), administered orally once daily.

The secondary objectives are:To evaluate the effect of the IMP on metabolic syndrome parametersTo evaluate the effect of the IMP on pro-inflammatory/inflammatory, fibrotic, diabetic, and obesity biomarkers in blood and urineTo evaluate the effect of the IMP on antidiabetic treatment, including oral therapy and insulin requirements

The exploratory objectives are:To examine the effect of the IMP on the histological appearances of fat biopsies, in particular the degree of fibrosis and macrophage infiltration;To analyse the effect of the IMP on the global metabolome using systemic blood and adipose tissue-specific microdialysis samples;To analyse the effect of the IMP on the microdialysate fractions using adipose tissue microdialysis samples;To assess the effect of the IMP on liver stiffness using transient elastography;To measure the effect of the IMP on the fat content and fibrosis burden in the liver using MRI;To measure the effect of the IMP on cardiac fibrosis and function using MRI and on biomarkers, including N-terminal pro-brain natriuretic peptide (NT-pro-BNP);To evaluate the effect of the IMP on additional pro-inflammatory/inflammatory, fibrotic, diabetic, and obesity biomarkers in blood and urine;To evaluate the effect of the IMP on glucose, insulin, and lipid dynamics using the hyperinsulinaemic-euglycaemic clamp test.

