### Study population and eligibility criteria

A total of 18 subjects will be enrolled. Subjects should fulfil the following criteria:16 years of age or older at screening;A diagnosis of ALMS, confirmed by genetic testing before screening;Subjects on diabetes treatment are receiving the same antidiabetic agent for a minimum of 1 month before screening;Able and willing to self-monitor blood glucose level with or without assistance;Female subjects of childbearing potential must have a negative pregnancy test and agree to use adequate birth control throughout the study and for 30 days after the last dose of study drug;Male subjects are willing to use an acceptable contraceptive method throughout the study and for 30 days after the last dose of study drug;Able to give written informed consent.

Subjects will not enter the study if any of the exclusion criteria listed in Additional file 3 is fulfilled.

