### Sample size and statistical analysis

This study is purely exploratory and aims to evaluate safety and tolerability of PBI-4050 and examine its effects on biomarkers. The study will collect data to derive descriptive statistics on secondary endpoints for future studies and no statistical hypothesis will be tested. A minimum of 8 subjects is deemed necessary in this part of the study. The data will be summarized using mean, standard deviation, median, and range. Demographic (sex, age, race, ethnicity, waist circumference, height, weight, and BMI) and baseline characteristics will be presented descriptively at baseline. Categorical variables will be reported as numbers and percentages. Paired t-test or where appropriate the non-parametric equivalent (Wilcoxon signed-rank test) will be used to compare variables before and after intervention. The Shapiro-Wilk test will be used to test the normality of the distribution. In the event that the normality assumption fails at the 0.10 alpha level of significance, the Wilcoxon Signed-Rank test will be used instead. Absolute values and changes from baseline in safety laboratory tests will be summarized by visit over time and presented in shift tables. To evaluate the shift over time, a mixed model comparing the slope before baseline (historical data) to the slope after baseline (on-treatment data) will be used. For comparing results of repeated samples, for example adipose tissue microdialysis where there are multiple time points during the same test, repeated measures analysis of variance will be used. All analysis will be conducted using SPSS statistical software. The significance level for this study is set at *p* < 0.05. All statistical analyses will be made using observed data. No imputation will be made.

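### HOMA2-B and HOMA2-IR are paired with fasting insulin and not with C-peptide, although insulin users are foreseeable, so in those subjects HOMA2-B would count injected insulin as beta-cell function

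*Protocol article*

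**What the plan says.** All references are to the protocol article.

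- **Measures.** Under Assessment of metabolic syndrome parameters and biomarkers, the parameters are "Fasting plasma glucose (FPG), Glycated haemoglobin (HbA1c), fasting insulin". As to timing, "FPG and fasting insulin will be measured every 12 weeks". The next sentence is "Homeostasis Model Assessment (HOMA2) for steady state beta cell function (HOMA2-B) and for insulin resistance (HOMA2-IR) will be calculated". It names no input and makes no exception for insulin users.
- **C-peptide.** It is listed later in the same section, in a paragraph that opens "Additional pro-inflammatory/inflammatory, fibrosis, diabetic and obesity biomarkers in blood (plasma) and urine will be measured for exploratory analysis". Nothing links it to HOMA2.
- **Insulin use.** Under Study objectives, one secondary objective is to evaluate "the effect of the IMP on antidiabetic treatment, including oral therapy and insulin requirements". The effect on metabolic syndrome parameters is another.
- **Eligibility.** "Subjects on diabetes treatment are receiving the same antidiabetic agent for a minimum of 1 month before screening". The condition concerns the agent, not the dose, and only the time before screening. Insulin is not among the prohibited medications under Intervention.
- **Analysis.** Under Sample size and statistical analysis, a paired t-test or a Wilcoxon signed-rank test "will be used to compare variables before and after intervention". Observed data are used, and no adjustment for antidiabetic therapy is mentioned. The trial has a single arm.

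**The concern.** A fasting insulin value in a subject who injects insulin can be the sum of two sources: the subject's own secretion and the injection. HOMA2-B is meant to describe the first. Computed from the sum, it credits the injection to the pancreas.

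The trial also expects that insulin requirements may change on treatment. If the injected part changes between baseline and Week 24, HOMA2-B changes with it even when own secretion does not. A reduced insulin requirement, which one secondary objective would count in the drug's favour, would then appear under another as lost beta-cell function. The opposite error is possible too: a real gain in own secretion can be hidden by a falling dose. With no control arm, nothing in the comparison absorbs these shifts.

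Beta-cell function matters to this trial. Table 1 names late pancreatic failure as a feature of the disease and sets against it preclinical maintenance or restoration of islet insulin content. HOMA2-B is the index in the metabolic set that speaks to this.

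**Working it through.** The article states no figure on this point, so there is none to reproduce. What follows shows direction and scale under stated assumptions.

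**Inputs**
- From the article: 18 subjects to be enrolled; a paired before-after comparison; no control arm.
- Assumed: *s*, the injected share of measured fasting insulin, 10% to 50%; *c*, the relative change in the injected part, -50% to +50%; 3 to 9 insulin users among the 18.
- Assumed: at fixed glucose, each index is proportional to measured insulin. HOMA2 has no closed form, so the first-generation formulas stand in for it: IR = G × I / 22.5 and B = 20 × I / (G - 3.5).

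**1. Overstatement of HOMA2-B at one visit.** Measured insulin = own / (1 - *s*), so the overstatement is 1/(1 - *s*) - 1.

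| *s* | 1/(1 - *s*) | Overstatement |
|---|---|---|
| 10% | 1.11 | 11% |
| 30% | 1.43 | 43% |
| 50% | 2.00 | 100% |

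**2. Before-after change in one insulin user.** With own insulin and glucose constant, measured insulin and both indices change by *s* × *c*. The extremes are 0.5 × (-50%) = -25% and 0.5 × (+50%) = +25%.

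**3. Worked example (all values assumed).** G = 8 mmol/L, own insulin 20 mU/L, injected part 10 mU/L, later halved to 5 mU/L.
- B: 20 × 30 / 4.5 = 133.3 falls to 20 × 25 / 4.5 = 111.1, that is -16.7%. Own insulin alone gives 20 × 20 / 4.5 = 88.9 at both visits, so the true change is nil.
- IR: 8 × 30 / 22.5 = 10.67 falls to 8 × 25 / 22.5 = 8.89, also -16.7%.
- Masking: if own insulin rose by the same 5 mU/L, the measured value would stay at 30 and B would not move, although own insulin rose by 5/20 = 25%.

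**4. Cohort mean.** With *u* users among 18 and the injected part halved in each, the mean of the per-subject changes is (*u*/18) × *s* × (-50%).
- 3 users, *s* = 20%: (3/18) × 0.2 × (-50%) = -1.7%.
- 6 users, *s* = 30%: (6/18) × 0.3 × (-50%) = -5.0%.
- 9 users, *s* = 50%: (9/18) × 0.5 × (-50%) = -12.5%.

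**5. Feasibility of C-peptide.** In Table 2, metabolic syndrome parameters are taken at Weeks 1, 12 and 24 and at extension visits 12, 24, 36 and 48. Biomarkers are scheduled at each of these visits, and concomitant medications are recorded there too.

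**The case against.** **The input is not stated.** The HOMA2 sentence does not name fasting insulin, and it does not say that the indices are calculated for every subject. A reader might infer that insulin-based indices for all subjects are laid down. They are not: both points are inferred from the order of the sentences and the absence of any restriction. The SAP and the exclusion criteria in Additional file 3 are not shown and may narrow this. That limits how firmly the point can be put. It does not remove it, because the article itself sets HOMA2 beside fasting insulin and puts C-peptide in a separate exploratory list. Excluding all insulin users would sit badly with an objective on insulin requirements.

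**A fall in HOMA2-IR may be real.** If glucose is unchanged while total insulin falls, less insulin is doing the same work, which is what lower resistance means. This stands. A reader might infer from the worked example that the change in both indices is wholly spurious; that holds for HOMA2-B but not for HOMA2-IR. The clamp also measures resistance at baseline and Week 24. It is exploratory and does not repair HOMA2-B, but conclusions on resistance do not rest on HOMA2 alone.

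**HbA1c and fasting glucose.** One might extend the argument to these, since therapy can change between visits. Comparing them as observed is a legitimate choice: therapy change is itself a secondary objective, and concomitant medication is recorded. Dropping values after a therapy change would select on a post-baseline event that may be related to response. No change is asked for here.

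**The trial is exploratory.** It is, and its primary objective is safety, which lowers the stakes. But the article says the descriptive statistics on secondary endpoints are meant for future studies, so a distorted HOMA2-B would be carried forward.

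**Conclusion.** The point holds for HOMA2-B in insulin users, and in weaker form for fasting insulin and HOMA2-IR in the same subjects. Read as it stands, the article would attribute injected insulin to beta-cell secretion and let the before-after change track the insulin dose.

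The size for this trial cannot be derived. The number of users, the injected share, the assay and the timing of the last injection are not given. The 11% to 100% range is a per-subject overstatement under an assumed share of 10% to 50%, and should not be read as the error in the trial's result. With a share of 20% to 50% and the injected part halved, the change in one user is -10% to -25%; with 3 to 9 users among 18, the mean change is about -1.7% to -12.5%. All of this rests on proportionality of the index to insulin at fixed glucose, which is an approximation for HOMA2.

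The consequence is moderate: a secondary index that would be hard to interpret in some subjects, with a better input already on the assay list.

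**What to change.** - State the HOMA2 input. Compute HOMA2, at least HOMA2-B, from the already planned C-peptide, measured in the fasting sample. For any subject on insulin at either of the two visits compared, use the same input at both.
- Report fasting insulin and insulin-based HOMA2-IR separately for insulin users and non-users, with the insulin dose at each visit next to the users' values.
- Check against the detailed schedules in Additional files 1 and 2 that C-peptide is assayed at every visit where HOMA2 is to be reported. Table 2 shows only a general biomarker row.

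C-peptide can remain an exploratory biomarker in its own right; naming it as the HOMA2 input does not require moving it to the secondary set.

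**Cost.** Mainly wording in the analysis plan, since the assay is already planned and biomarker sampling coincides with the metabolic visits. The insulin-based summaries will rest on fewer subjects, which is a real loss with 18. Grouping by insulin use at either visit depends partly on a post-baseline event, so the split summaries should be read as descriptive.

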#### Assessment of liver fibrosis

Transient Elastography (TE) is one of several methods, including liver MRI and the enhanced liver fibrosis (ELF) test, to measure the presence of liver fibrosis and response to PBI-4050. TE is a non-invasive technique to assess liver stiffness by measuring the velocity of sheer waves through the liver [26–28]. TE is performed using a Fibroscan (Echosense, France) with an M-probe (3.5 Hz frequency) or XL-probe (2.5 Hz frequency). All assessments are performed in the dorsal decubitus position with the ultrasound probe tip overlying the right lobe of liver [29].

MRI of the liver will be used to quantify liver fibrosis and response to PBI-4050. Using a 1.5 T (Siemens Avanto) scanner, the sequences acquired include 1) a central slice Shortened Modified Look-Locker Inversion recovery T1 sequence that times the longitudinal relaxation of each imaged voxel; 2) a multi-slice Spin Echo Imaging Inversion Recovery T1 mapping sequence; 3) a central slice high resolution T2 sequence that times the transverse relaxation of each imaged voxel; and 4) a central slice Dixon sequence that is used to separate water and fat.

An Enhanced Liver Fibrosis (ELF) test will be performed. The ELF test consists of three serum biomarkers and correlates with levels of liver fibrosis [30].

#### Assessment of cardiac fibrosis

Cardiac MRI will be used to quantify cardiac fibrosis and response to PBI-4050. Using a 1.5 T (Siemens Avanto) scanner left and right ventricular volumes, mass and function will be acquired using standard protocols. T1 mapping will be performed before and after gadolinium contrast using a Modified Look Locker Inversion recovery sequence employing a 5 s(3 s)3 s sampling protocol (average breath hold 10–15 s) to quantify diffuse myocardial fibrosis. Late gadolinium enhancement imaging will be performed 7–10 min after 0.15 mmol/Kg of gadolinium contrast bolus (Gadovist Bayer Health Care) to quantify extent of coarse replacement fibrosis [31].

#### Assessment of adipose tissue

Adipose tissue samples will be used to quantify the effects of PBI-4050 on fibrosis in adipocytes. Subcutaneous adipose tissue from ALMS subjects is to be characterised using histo-morphometry and immunohistochemistry staining. The biopsies are collected from the abdomen on the lateral side of the umbilicus on the abdominal wall. After administration of local anaesthetic (1% lignocaine), a 1-cm subcutaneous incision is made with a scalpel and the removed sample of adipose tissue is immediately preserved in 2 parts in formalin and RNAlater® Stabilization Solution (Thermofisher scientific). The samples stored in formalin are then embedded in paraffin to make formalin-fixed paraffin-embedded (FFPE) blocks. The FFPE blocks are cut and stained with haematoxylin and eosin and picrosirius-red staining for quantification of adipose tissue fibrosis. Adipocyte size is measured by means of light microscopy. Immunohistochemistry with macrophage, T-cell and collagen markers will be performed to quantify inflammatory activity and collagen deposition. Global gene expression in adipocytes will be measured. Adipose tissue stored in RNAlater is prepared using RNeasy Lipid Tissue (QIAGEN) and next generation gene sequencing performed to access expression of pro-fibrotic genes.

Adipose tissue microdialysis is used to sample interstitial fluid intermediary metabolites in the form of glycerol, glucose, pyruvate and lactate, which act as a marker of adipose tissue lipolysis. A microdialysis catheter (CMA microdialysis [CMA 106/107], Sweden) is inserted approximately 10 cm lateral to and at the level of the umbilicus via a subcutaneous incision after local anaesthetic (1% lignocaine). Samples are collected every 30 min into micro-vials (0.3 μL/min) until the end of the hyperinsulinaemic-euglycaemic glucose clamp.

#### Assessment of insulin secretion and resistance

The hyperinsulinaemic-euglycaemic glucose clamp is considered the gold standard for quantifying insulin secretion and resistance and will be used to monitor the effects of PBI-4050 on insulin resistance in ALMS [32]. In effect, blood glucose lowering effects of insulin are antagonised by glucose infused at a variable rate to keep blood glucose clamped at a specific fasting level [33].

Subjects are required to fast overnight before starting the hyperinsulinaemic-euglycaemic clamp at 0900 am the following morning. Fasting glucose is recorded and subjects are then clamped at that level. Subjects are given a bolus (2 mg/kg) of D-Glucose (U-13C6) (Cambridge Isotope Laboratories, UK) before a continuous infusion of D-glucose (20 μg/kg/min) for the next 4 h. An infusion of potassium palmitate 2, 2 D2 (Cambridge Isotope Laboratories, UK) in 5% albumin (0.03 μmol/kg/min) is given at the same time and continues for next 4 h until the end of procedure. During the first 2 h (basal phase), blood glucose is checked every 15 min and additional bloods are taken at time points 0, 90, 105, and 120 min for measurement of insulin, free fatty acid and stable isotopes for the assessment of whole body basal glucose turnover. Samples taken at time points 0, 90, 105, 120, 210, 225 & 240 will also be analysed with another reference laboratory method and clamp quality for these paired samples reported according to Benesch et al., 2015.

Insulin (Actrapid; Novo Nordisk, Copenhagen, Denmark) infusion is then started at 120 min at a rate of 40 mU/m^2^/min. Four minutes later, a 20% dextrose solution with [^13^C]-glucose (enriched to 4%) is commenced at time point 124 min. During the insulin-stimulated state period, blood sugars are checked every 5 min to allow for dextrose infusion rate adjustments to maintain fasting glycaemic levels. At time points 210, 225 and 240 min, steady state blood samples are collected. The rates of endogenous glucose production, glucose disposal and lipolysis (Rd - rate of disposal of palmitate) are calculated.

### Discontinuation or withdrawal of study subjects

PBI-4050 will be permanently discontinued for the following reasons:Subject’s withdrawal of consent;An AE, which in the opinion of the investigator warrants discontinuation of treatment;Pregnancy;Death;Substantial protocol deviation;Investigator’s decision;Sponsor’s decision;Subject starting a prohibited therapy (see Section 5.6);aspartate transaminase or alanine transaminase rises to > 5 × upper limit of normal;A drop in heart rate from baseline by 15 beats per minute that is associated with clinically relevant cardiovascular symptoms as determined by the investigator;A drop in systolic blood pressure by 20 mmHg or diastolic blood pressure by 15 mmHg from baseline that is associated with clinically relevant cardiovascular symptoms as determined by the investigator.

Subjects who discontinue study treatment but have not withdrawn consent will be asked to attend the appropriate End-of-Treatment and End-of-Study visits, depending upon whether they withdraw before or after Week 24. Subjects who withdraw consent will not have further study-related information collected for the clinical trial database, with the exception of follow-up on on-going AEs or any new AEs within the safety follow-up period. Subjects who withdraw due to AEs will be followed until the event has resolved or stabilized.

In the case of any substantial deviation from the protocol, the investigator and sponsor will decide on the further participation of the subject in this study, having discussed all relevant aspects. The sponsor may discontinue the study in its entirety before its completion for reasonable cause, provided that written notice to the investigator, regulatory authorities and independent ethics committee (EC) is submitted in reasonable time in advance of the intended termination.

If subjects decide to enter the ALMS rollover study (Study PBI-4050-CT-9-10) after completing the 36- or 48-week extension period, then they will sign an informed consent for that study and stop participation in the current study.

### Pharmacovigilance and data monitoring

All SAEs will be reported to pharmacovigilance/safety personnel within 24 h after the investigator becomes aware of the event. All relevant information about any suspected unexpected serious adverse reaction (SUSAR) occurring during the course of a clinical trial and if fatal or life-threatening will be reported as soon as possible and in any event not later than 7 days to the competent authority. All SUSARs occurring in the interventional study will be entered into a European database established in accordance Directive 2001/20/EC and reported to the relevant ECs. A Data Safety Monitoring Board will review individual subject safety data in an on-going fashion. An unaffiliated clinical research associate will monitor the data collected throughout the study, thus providing quality control (QC) of the study and QC of the database and data management.

